### Interventions

#### FAST

The treatment stage of FAST lasts five to nine months depending on the individual goals of the juvenile and the caregiver(s) and is followed by a period of aftercare (for more information on the treatment stages of FAST, see Table 2). At the start of treatment, therapists write an individualized basic Empirical Intervention cycle Summary (EIS). In the basic EIS, a problem analysis or function analysis of the problem behavior is described. The recidivism risk is determined and the safety for the juvenile, caregiver(s), and therapists and the degree of motivation are described. The basic EIS describes which FAST sub-goals need to be targeted to realize the main goal of FAST. During treatment, therapists evaluate the EIS every two weeks with the juvenile and the caregiver(s) and discuss which general and optional FAST sub-goals have the most priority. Interventions are selected based on the chosen sub-goals and by applying analysis circles. An analysis circle is created around a problem that is related to the chosen FAST sub-goal: On the right side of the circle, the influencers that contribute negatively to the problem behavior, or increase the problem behavior are described; on the left side of the circle, the influencers that reduce the problem behavior are described. Influencers can originate from various systems around the juvenile and family and are introduced by the juvenile and caregiver(s) themselves. When it is determined that the chosen sub-goals are reached, new goals are prioritized and new analysis circles are made. During treatment, the following supplementary modules can be selected for individual treatment: Stress and anger reduction, Impulse control, Self-control, Perceiving and interpreting correctly, Emotion-regulation, and Self-image. Every two months an evaluation takes place to determine whether longer treatment is needed with a maximum of nine months. In the last stage of the treatment, a future plan is developed that aims to prevent relapse.

**Table 2 Tab2:** Treatment Stages of Forensic Outpatient Systemic Therapy (FAST) and Differences and Similarities Between FASTb and FASTr

Stage (duration)	Content	Differences and similarities between FASTb and FASTr
1. Preliminary referral (one month)	During this stage, all information needed to start a FAST trajectory is gathered by the professional. This phase consists of the registration, including viewing file information, contacting the referrer, and taking care of an intake interview. The intake interview takes place at the homes of the client and his/her caregiver(s) or at the treatment site of de Waag.	Intake is face-to-face in both conditions.
2. Pre-treatment (one month)	During this phase, making contact and motivation are central concepts. This phase is aimed at establishing contact, motivating, empowerment, making a safety plan and drawing up a treatment plan in the form of an Empirical Intervention Cycle Summary (EIS). In the EIS, a problem analysis is described, the recidivism risk is established and then monitored, as are motivation and safety for the juvenile, caregiver(s) and professionals. Every two weeks, the family discusses which general or optional sub-goals have the highest priority. At least three goals are worked on every two weeks. Preferably, attention is paid to realizing changes aimed at the family/ caregiver(s) in combination with changes aimed at the social domain (education and contact with friends) and individual domain (criminogenic needs) of the juvenile. When the sub-goals are met, new FAST goals are prioritized. In addition, professionals always pay attention to what is needed to guarantee or improve the safety of everyone and received support of the family members. An important goal is to improve the quality of contact and to reduce conflicts between caregiver(s) and the juvenile. Next, analysis circles are used to determine which interventions are most appropriate and will be implemented over the next two weeks.	First appointment after intake is face-to-face in both conditions.
3. Treatment (two to eight months)	In this stage, customized treatment is offered by working on standard FAST and optional FAST goals (addressed in supplementary modules). Regular FAST treatment consists of the Family-module, which first focusses on safety and connection, by using safety and crisis plans, and by learning to use a signaling plan. In addition, social support is organized via the network of the family. Second, parenting skills are improved. Selection of specific family modules is based on the needs of the caregiver. To do so, the EIS is evaluated and, if needed, changed every two weeks with the family and during the FAST intervision to determine the quality and to monitor the progress of the treatment. It is also assessed whether the interventions have actually led to change or whether they should be applied for a longer period of time	FASTr does not make use of eHealth or the GRIP-app. In FASTb, family modules are offered (partly) through Minddistrict.
4. Completion	The goals of the FAST treatment that were applicable to the juvenile and the family have been (largely) achieved. This will be confirmed by the presence of a future plan (focused on relapse prevention) and achieved results that are recognized by the FAST professional, the caregiver(s), referrer, and the juvenile.	The final session is face-to-face in both conditions.
5. Aftercare (one to three months, depending on risk level)	In the aftercare phase, the family works on their future plan with the support of significant others in their environment. In this phase, the FAST professional checks whether the juvenile and caregiver(s) are able to adhere to the plan for the future and whether the results can be maintained. Aftercare sessions will take place monthly.	Aftercare is completely online in FASTb, unless necessary to meet clients face-to-face.

Within FAST, treatment integrity is monitored closely. Every FAST therapist has succeeded the FAST basic training and offers FAST minimally 20 h per week. Each team has weekly FAST team meetings, during which treatments are monitored by evaluating the EIS’ and a bi-monthly treatment checklist, guided by an appointed therapist that is responsible for treatment integrity. At the end of the treatment, the FAST evaluation forms are completed by juveniles, caregivers, and therapists to verify compliance with the most essential FAST methods and techniques.

#### FASTr-condition

FASTr includes around 3 hours of face-to-face direct treatment time weekly. It consists of a maximum of 10% online direct treatment time, i.e., treatment via phone, video-calling or texting.

#### FASTb-condition

FASTb consists of a minimum average of 50% online direct treatment time over the duration of the intervention, such as phone calls, video calls, text messages, and eHealth. For more information on differences between FASTr and FASTb, see Table 2. eHealth involves the use of the software platform Minddistrict and the GRIP-app, a simple app which is combined with a heart rate watch on the client’s mobile telephone that registers physiological aspects of stress and anger and warns clients when they get aroused.

### Measures

An overview of the various constructs, informants and timing of assessments is presented below and provided in Table 1. Self-report and case file data will be collected. Case file analysis includes the retrieval of self-report questionnaires that are filled out by juveniles, caregivers and/or therapists as part of the standard FAST procedure, next to the coding of client information such as primary diagnosis (see below).

#### Primary outcomes

##### Externalizing behavior

Externalizing behavior will be measured at T1, T2, and T3 using juvenile self-report on the Externalizing scale of the Youth Self Report (YSR) [43] and caregiver report on the Child Behavior Checklist (CBCL) [44]. Both the YSR and CBCL contain 33 items, which are rated on a 3-point Likert scale ranging from 0 = *never* to 2 = *often*.

##### Delinquency

Delinquency will be measured at T1, T2, and T3 using juvenile self-report on the Self-report delinquent behavior (SDB) [45]. The SDB contains 30 items, asking the respondent to state the number of times they did certain things in the past year.

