### Procedure

During the intake, therapists evaluate whether the clients meet the inclusion and exclusion criteria for the study. In case of doubt, therapists consult the research team in order to determine whether exclusion criteria are met. Once determined that a family can start FAST treatment, therapists ask caregivers and juveniles permission to share their contact details with the researcher. If they agree, FAST clients are approached by the main researcher or research assistants, whom all have signed a non-disclosure agreement and provided a certificate of conduct. Eligible clients receive verbal and written information about the study. The researcher obtains written informed consent from juveniles and caregivers for own participation, and from caregivers/legal representatives for juveniles younger than 16 years. After obtaining informed consent, participating families are randomized to receive FASTb or FASTr. Randomization is done on the level of the treatment site using a computerized randomization in a 1:1 ratio. Randomization outcome is shared by the researcher with both participants and participants’ therapist.

During the study, participants (juveniles and caregivers) fill out main questionnaires three times: Prior to or during the first weeks of intervention (pre-test; T1), immediately after the intervention (post-test; T2), and 6 months after termination of the intervention (6 months follow-up; T3). Therapists fill out questionnaires at T1 and T2. In addition, during the intervention, juveniles and caregivers fill out short monthly questionnaires. The number of monthly questionnaires depends on the length of intervention, which differs between five and nine months. Further, case file analysis is used to retrieve questionnaires that are filled out by juveniles, caregivers, and therapists as part of the standard FAST procedure. Official recidivism data will be collected at two-year follow-up (T4) to determine longer-term effects. For an overview of the study, see Fig. 2.

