#### Effectiveness

Research questions related to the effectiveness of FASTb versus FASTr on the primary and secondary outcomes will be answered using co-variance analyses with a correction for multiple testing, with the pre-test (T1) score on the dependent variable as a covariate, the post-test (T2) and 6-month follow-up (T3) scores as the dependent variable, and the condition (FASTb or FASTr) as a factor. Dichotomous outcome variables will be tested with Chi-square analysis to compare the percentage of the FASTb and FASTr conditions. Recidivism data after two years (T4) will be analyzed using Kaplan Meyer and Cox survival analyses. Effect sizes will be computed as Cohen’s d, based on adjusted means and standard errors.

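### Past-year recall makes 25–58% of the post-test delinquency window pre-treatment time, which shrinks the T2 arm difference toward equality

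*Protocol article*

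**What the plan says.** The Delinquency section of the protocol article gives the SDB to juveniles at T1, T2 and T3. It describes the instrument as 30 items, "asking the respondent to state the number of times they did certain things in the past year". No other recall period is given for T2 or T3. The section on monthly assessments does describe how the SDB is changed for monthly use (six items, some of them composites).

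The Procedure section places T1 "Prior to or during the first weeks of intervention (pre-test; T1") and the later waves "immediately after the intervention (post-test; T2), and 6 months after termination of the intervention (6 months follow-up; T3"). It also gives the course length: "The number of monthly questionnaires depends on the length of intervention, which differs between five and nine months". The FAST section repeats the range of five to nine months.

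Under Effectiveness, the T2 and T3 scores are dependent variables in covariance analyses with the T1 score as covariate. The Aims section and the Discussion expect the two versions of FAST to be equally effective.

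**The concern.** A twelve-month question asked at the end of a course of five to nine months reaches back before the course began. Acts from those earlier months cannot reflect the assigned version of FAST. Randomization makes them equal in expectation, and T1 has already counted them. They add the same expected amount to both arms at T2 and pull the arms' T2 scores together.

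In a trial designed to show that one arm is better, such dilution would be conservative. Here the expected result is equality, and the article's conclusion turns on blended treatment being no worse than face-to-face treatment. A real disadvantage of FASTb on delinquency during treatment could be understated at T2 and read as support for the hypothesis.

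**Working it through.** The article gives no figure for this overlap, so there is none to reproduce.

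**Inputs from the article.** Recall window: 12 months. Course length D: 5 to 9 months. T1 at the start of the course, T2 at its end, T3 six months after its end.

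**Pre-treatment share.** At T2 it is (12 − D)/12. At T3 it is max(0, 12 − D − 6)/12. If the arms differ by a constant monthly amount from treatment start, the T2 mean difference is D/12 of its size in a 12-month window lying wholly after treatment start.

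| D (months) | T2 pre-treatment share | T2 difference kept | T3 pre-treatment share |
|---|---|---|---|
| 5 | 7/12 = 58% | 5/12 = 42% | 1/12 = 8% |
| 7 | 5/12 = 42% | 7/12 = 58% | 0 |
| 9 | 3/12 = 25% | 9/12 = 75% | 0 |

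**Overlap of T2 and T3.** Counting from treatment start, the T2 window runs from D − 12 to D and the T3 window from D − 6 to D + 6. They share six months.

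**Effect on a ratio of rates (assumed values, illustration only).** Let FASTr reduce the monthly rate to a fraction q of its earlier level, and let the FASTb rate during treatment be 1.5 times the FASTr rate. The ratio seen at T2 is [(12 − D) + 1.5qD] / [(12 − D) + qD].

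- q = 0.6: 11.5/10 = 1.15 (D = 5), 11.3/9.2 = 1.23 (D = 7), 11.1/8.4 = 1.32 (D = 9).
- q = 0.7: 12.25/10.5 = 1.17, 12.35/9.9 = 1.25, 12.45/9.3 = 1.34.
- At T3 with q = 0.6: (1 + 0.9 × 11)/(1 + 0.6 × 11) = 10.9/7.6 = 1.43 at D = 5, and the full 1.50 from D = 6.

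**Does the T1 covariate repair it?** T1 has the same expectation in both arms, so a linear adjustment for it leaves the expected arm difference unchanged. It removes some of the noise from the earlier months but not the attenuation.

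An illustrative simulation agrees. It used 100 per arm, overdispersed Poisson counts, 0.5 acts per month before treatment, q = 0.7, a true ratio of 1.5, ANCOVA on log(1 + count) with T1 as covariate, and 1,500 runs per D. Power at T2 for D = 5, 7 and 9 was:

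- past-year window: 0.51, 0.65, 0.75;
- window limited to the treatment period: 0.71, 0.77, 0.82.

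The loss is therefore about 0.20 for a five-month course and 0.07 for a nine-month course under these assumptions.

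**The case against.** The strongest reply is that this affects one wave of one outcome. The YSR, the CBCL, out of home placement, RAF GGZ Youth recidivism risk and T4 convictions are also primary and do not use this past-year item frame. The SDB is analysed at T3 as well, and six SDB items are collected monthly during treatment. All of this stands, and it limits the severity. The monthly items do not remove the problem, because the abstract and the Design section assign the monthly assessments to mechanisms of change.

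The sizes of effect above also rest on assumed rates and on a full effect from the first day. That is fair. The shares of 25% and 58% do not depend on those rates, nor does the direction of the shrinkage.

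Several stronger readings are tempting, but the article does not support them:

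- **T3 is diluted too.** About half of the T3 window is treatment time, but those are months in which the arms can differ. Only 0–8% is pre-treatment. T3 repeats six months of the T2 window, but the article does not claim that the two waves cover separate periods.
- **Up to nine of twelve months are pre-treatment.** This comes from adding one month of pre-treatment to the shortest stage in Table 2 ("3. Treatment (two to eight months"). The Procedure and FAST sections both state five to nine months, and Table 2 gives the completion stage no duration.
- **A skewed count is put into a linear ANCOVA.** A reader might infer this from "Dichotomous outcome variables will be tested with Chi-square analysis", since no other exception is made before T4. The article does not say how the SDB is scored or transformed, and an analysis plan commonly settles that.
- **Dilution differs by arm.** Both arms have the same stated range of duration, so this is a possibility only.

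**Conclusion.** The point holds for T2. With a past-year frame and T2 at the end of a course of five to nine months, 58% to 25% of the T2 window is pre-treatment time already counted at T1. The T2 mean difference keeps about 42% to 75% of its full-window size. Adjustment for T1 does not restore it, and the shrinkage runs toward the hypothesised result. T3 is essentially unaffected.

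This rests on three assumptions: T2 precedes aftercare, as the Procedure section indicates; the past-year wording is used unchanged at T2, as the Delinquency section states; and, for the 42–75% figure, the monthly arm difference is constant from treatment start. If T2 instead followed the one to three months of aftercare, the share would run from (12 − 5 − 1)/12 = 50% down to (12 − 9 − 3)/12 = 0.

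It should be fixed, but it does not undermine the trial as a whole, since it concerns one wave of one of several primary outcomes.

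**What to change.** **From now on.** At T2, ask about the period since the T1 assessment and record the months covered. Analyse the T2 score as a rate, or adjust for months covered. Keep the past-year frame at T1. Anchoring on the T1 assessment rather than on the start of FAST matters because T1 may fall some weeks into the course, and those weeks would otherwise be counted twice.

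**For participants already assessed at T2 with the past-year frame.** The count cannot be split afterwards. Flag which frame was used, treat their T2 SDB contrast as attenuated, and do not take a null T2 SDB result as evidence of equal effectiveness. Rest the SDB conclusion on T3. The six monthly items can serve only as a supportive during-treatment measure, because they are abbreviated and capped at more than 10 times.

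**Cost.** A changed instruction at T2, one extra recorded field and an amendment. The T2 score departs from the past-year reference period, and early and later participants will have different T2 frames, which the analysis and the report must show. A shorter window also counts fewer acts. In the illustration, power with the treatment-period window (0.71 to 0.82) stays below the 0.84 of a full year after treatment start, so the change recovers part of the lost information and not all of it.

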##### Out of home placement

Out of home placement will be coded from case files at T1 and T2 and will be measured at T2 and T3 by juvenile and caregiver report on a questionnaire measuring living situation. Four items assess where the juvenile lives most days of the week, which will be recoded into the categories 0 = *no* and 1 = *yes*.

##### Recidivism risk

Recidivism risk will be measured at T1 and T2 using the RAF GGZ Youth [39], which is filled out by therapists as part of the standard FAST procedure. Recidivism risk is rated on a 5-point Likert scale ranging from 1 = *low* to 5 = *high*.

##### Recidivism

Recidivism will be measured at T4 by coding if, when, and what type of crime juveniles were convicted for from official judicial records.

#### Secondary outcomes

##### Substance use

Substance use will be measured at T1, T2, and T3 using juvenile self-report questionnaire ‘Peilstation Middelengebruik’ [46] and case file analysis of the RAF GGZ Youth [46] and the FAST Goal lists. The Peilstation Middelengebruik contains five items measuring frequency and intensity of substance use (alcohol and drugs). The RAF GGZ Youth includes six items investigating the substance use of the juvenile. These items are summarized into a clinical judgment score ranging from 0 = *the client has no problem with alcohol and/or drug abuse now or in the past* to 5 = *the client currently has severe issues related to alcohol and/or drug abuse or dependence*. The FAST Goal lists are filled out by the juveniles, caregivers, and therapists, and contain one item investigating whether the juvenile uses substances (drugs or alcohol) and whether it leads to problems. The item is rated on a 10-point Likert scale ranging from 1 = *completely not true* to 10 = *completely true*.

##### Contact with deviant peers

Contact with deviant peers will be measured using juvenile self-report at T1, T2, and T3 on the Basic Peer Questionnaire (BPQ) [47]. The BPQ contains six items, which are rated on a 4-point Likert-scale ranging from 1 = *none* to 4 = *almost all of them*.

##### Client formulated goals

 Client formulated goals will be measured at T1 and T2 using case file analysis of the FAST Goal lists, which are filled out by juveniles, caregivers, and therapists as part of the standard FAST procedure. The FAST Goals lists consists of 21 items and provides a subjective measure of the effectiveness of FAST by asking respondents to rate whether they have reached the goals of FAST. The items are rated on a 10-point Likert scale ranging from 1 = *completely not true* to 10 = *completely true*.

#### Mechanisms of change

##### Social support

Social support will be measured at T1, T2, and T3 using caregiver self-report on the Parental Support Questionnaire (PSQ) [48]. The questionnaire contains 15 items, asking participants from whom or what they receive support (0 = *no* and 1 = *yes*) and, if they do, to rate their support satisfaction on a 5-point Likert scale ranging from 1 = *unsatisfied* to 5 = *satisfied*.

##### Family functioning

The following indicators of family functioning will be assessed: caregiver-juvenile conflict and relationship quality, caregiver behavior, and caregiver competence.

Caregiver-juvenile conflict will be measured at T1, T2, and T3 using juvenile and caregiver report on the Network of Relationship Inventory (NRI) [49]. The NRI contains six items, which are rated on a 5-point Likert scale ranging from 1 = *little to none* to 5 = *the most*.

Caregiver-juvenile relationship quality will be measured at T1, T2, and T3 using juvenile report on the Attachment scale of the Inventory of Parent and Peer Attachment (IPPA) [50, 51] and caregiver report on the Nijmeegse Parenting Stress Index (NPSI) [52]. The IPPA Attachment scale contains 12 items, which are rated on a 4-point Likert scale ranging from 1 = *almost never* to 4 = *almost always*. The NPSI Attachment scale contains 9 items, which are rated on a 6-point Likert scale ranging from 1 = *totally disagree* to 6 = *totally agree*.

Caregiver behavior will be measured at T1, T2, and T3 using juvenile and caregiver report on the Responsiveness and Consistency scales of the Nijmeegse Parenting Questionnaire (NPQ) [53], the Behavioral Control scale of the Parenting Practices questionnaire [54], three hypothetical situations from the Parenting Dimensions Inventory (PDI) [55] of which mean scores of two items measure Inductive Discipline, two items measure Harsh Discipline, and three items measure Other Punishments, and juvenile report on the Psychological Control Scale Youth Report (PCS-YR) [56]. The Responsiveness and Consistency scales of the NPQ contain 16 items, which are rated on a 6-point Likert scale ranging from 1 = *totally disagree* to 6 = *totally agree*. The Behavioral Control scale of the Parenting Practices contains six items, which are rated on a 5-point Likert scale ranging from 1 = *never* to 5 = *always*. The items on the PDI are rated on a 6-point Likert scale ranging from 1 = *very improbable* to 6 = *very probable*. The PCS-YR contains eight items, which are rated on a 6-point Likert scale ranging from 1 = *completely disagree* to 6 = *completely agree*.

Caregiver competence will be measured at T1, T2, and T3 using caregiver self-report on the Competence scale of the NPSI [60]. The scale contains 15 items, which are rated on a 6-point Likert scale ranging from 1 = *totally disagree* to 6 = *totally agree*.

